## Abstract

**Background:**

The prevalence of non-communicable diseases (NCDs) is increasing in the world. Healthy food choice and adequate physical activity are key factors in preventing NCDs. Food labeling is a strategy that can inform consumers to choose healthier foods at the point of purchase. In this study, we intend to examine the status of existing labels and to clarify their strengths and weaknesses. Then, for the first time in Iran, we will design a type of physical activity equivalent calorie label and will test it on some food groups of packaged products including dairy products, sweetened beverages, cakes, and biscuits.

**Methods:**

This study will be conducted in two phases. In phase 1, nutrition fact labels and traffic light labels will be assessed through focus group discussions and interviews among different groups of mothers, industrialists and nutrition and food industry specialists as to determine strengths and weaknesses of the current labels on packaged products. Then, the initial layout of the physical activity calorie equivalent label will be drawn with respect to the viewpoints received from mothers. Thereafter, we will include the scientific opinions to it for creating the first draft of our new label. In phase 2, a total of 500 mothers of students 6–12 years old randomly assigned to five groups. The study groups will be as follows: (1) without nutrition label group, (2) current traffic light label group, (3) current traffic light label group in which, a brochure will be used to inform mothers, (4) physical activity calorie equivalent label group, and (5) physical activity calorie equivalent label group in which a brochure will be used to inform mothers. Some samples of dairy products, beverages, cakes, and biscuits will be presented. ANOVA and multiple linear regressions will be used to examine the association between the label type and the main consequence (energy of the selected products) and secondary outcome (time).

**Discussion:**

The effect of the new food labels will be evaluated based on the differences between the calories of selected food groups.

**Trial registeration:**

Iranian Registery of Clinical Trials [IRCT]20,181,002,041,201 N1.

## Background

The global prevalence of non-communicable diseases (NCDs) is increasing, particularly in low- and middle-income countries [1]. The World Health Organization estimated that 39% of adults aged ≥18 years were overweight and 13% were obese in 2016 [2].

According to the available scientific evidence [3–5], major NCDs, other than road injuries can be reduced through healthy nutrition. In addition, long-term strategic policy-making can reduce the increasing trend and excessive costs of NCDs [3].

Food environment policies can affect all people, because they have influence on behavior and can make a great part of daily choices [6]. In this regard, environmental changes and policy-making should be accompanied by programs that motivate people and enable them to choose healthier foods and improve their physical activity [7]. Globally, there are various policies to modify people’s eating behaviors. Such policies include food labeling [7–9], taxes and subsidies [9], and marketing and quality standards [10, 11].

Food and meal labeling have been established with the aim of influencing consumers’ choices [12]. The effectiveness of food labels has been studied over various durations [13, 14] through randomized [15, 16] and non-randomized [17, 18] interventions. Most studies in this regard have been carried out in high-income countries such as North America and Europe [19, 20].

In Iran, various labels including nutrition information have been used for over 10 years. Starting from 2014, traffic light labeling on food products had been optional by the Food and Drug Administration of Iran, but it became mandatory for all packaged products after 2 years [21]. The results of a review of the data from United States and Canada suggest the use of a traffic light on packaged products might be helpful [22]. The effectiveness of such labels has not been checked in Iran yet [23].

One of the newer types of labeling recently introduced shows the amount of physical activity including distance or time needed to burn off the calories in a food item [24]. Based on the data of three focused group discussions (FGDs) data, Dowray et al. designed physical activity calorie equivalent labels for the consumer and tested them in a hypothetical scenario study. In that cross-sectional study, calorie content of the selected fast food meals was defined as the outcome. Two types of physical activity label were designed that had presented the amount of miles or minutes needed to burn off calories. A label displaying physical activity in distance had the greatest influence. However, most participants preferred a label expressing physical activity in minutes required to burn calories as opposed to distance. At the end, 82% of the subjects preferred a physical activity calorie equivalent label [24]. In the study by Antonelli et al. 80% of participants believed that a physical activity calorie equivalent label could affect their dietary choices and also increased their motivation for physical activity [25].

Therefore, this study will be conducted to investigate the status of packaged products in Iran, including traffic light food label and nutrition information label, to identify their strengths and weaknesses. Another important objective of current study is to design a physical activity calorie equivalent label considering views of consumers, experts, and executives for the first time in Iran. Then, the new physical activity equivalent calorie label will be compared with current traffic light food label of packaged products. To achieve this, the products will be presented with either the new designed physical activity label or the current traffic light label to determine the effects of these labels on food choices.

## Methods and design

This study will be conducted in two phases.

### Phase 1

#### Step I: assessing of existing labels on packaged products

For step I, during a thematic analysis, all types of labeling covering nutritional information and traffic light labels will be assessed through FGDs and interviews with different groups of mothers, nutrition and food industry specialists, and industrialists. To gather mothers’ opinions from five different regions (North, South, East, West, and Central), the current map of 22 municipal districts of Tehran will be used. First, five districts out of 22 will be randomly and then two elementary schools (6–12 years) will be selected from each of those 5 districts (a total of 10 elementary schools). Using the available list of schools in the Education Department of selected regions simple randomization. Thus, 10 elementary schools will be chosen and at least ten FGDs will be held in those selected schools. To invite participants, the mothers will be contacted by phone up to when 6 of them accept to co-operate. Homogeneous purposeful sampling regarding education level will be used [26]. On the day that FGD will be conducted, the investigator will introduce herself and the note taker as well as the aim of this study. Then consent form will be signed by mothers and a demographic questionnaire will be completed by face to face interview. All FGDs will be recorded by a voice recorder and a note taker takes all the discussions during the sessions. Each session will consist of two parts: in the first part, the Iranian existing “traffic light label” and “nutrition fact label” will be discussed in order to clarify the strengths and weaknesses. The Iranian Ministry of Health has duty to check the accuracy of current labels provided by factories and we trust those information. Thus we will not try to check such information in our current study.

In the second part, the concept of a physical activity calorie equivalent label will be introduced and we will ask the participants for their opinions about it, and necessary information will be obtained. The length of these sessions will be 90 min.

After FGDs conducted with mothers, while summarizing the FGDs findings, at least six semi-interviews will be conducted with quality managers and industry experts from different groups of dairy products, cakes, biscuits and sweetened beverages. Before interviews, a semi-structured questionnaire will be designed by the investigator. The purposeful snowball sampling will be applied [26]. In this regard, subjects from famous brands will be interviewed and the interviewees will recruit other experts according to the aim of the study. Before conducting the interviews, the interviewees will be aware of the purpose of the research and the interviews will be recorded by a voice recorder after asking for their permission. Furthermore, participants will be assured that the information would be used only for research purposes and would not be accessible for others who are not in the research team.

As the final activity of step I, the results of mothers’ FGDs and industrialists’ interviews will be presented to a group of nutritionists and food industry experts in separated FGDs through a short 10-min presentation. In FGDs with nutritionists and food industry experts, the strengths and weaknesses of traffic light label and nutrition fact label will be identified, the expectations of mothers regarding the physical activity calorie equivalent label will be discussed, and the experts’ comments will be collected.

#### Step II: designing the new label based on physical activity calorie equivalent

In step II, the initial layout of the physical activity label will be drawn by a graphic artist with respect to the viewpoints of the mothers. The label will be changed by consensus among researchers based on the mothers’ and experts’ opinions. Ultimately, the final version. of physical activity calorie equivalent label will be designed.

As step II, the initial layout of the physical activity label will be drawn by a graphic artist with respect to the viewpoints received from all 3 groups. Thereafter, the first draft of the Physical Activity designed label will be emailed to mothers participated in FGDs asking for their opinions. The label will be changed by consensus among researchers based on mothers and experts’ opinions. Ultimately, the last version of physical activity calorie equivalent label will be designed.

### Phase 2: intervention

Similar to phase 1, 10 elementary schools will randomly be selected from five districts of Tehran. The mothers of children from these schools will be recruited to assess the effect of the new label. To invite the participants, the mothers will be contacted by phone, until 50 literate mothers accept to cooperate. After obtaining informed consent, demographic data will be collected and mothers will be asked to complete the International Physical Activity Questionnaire (IPA) [27] in order to determine whether they have any especial interest in physical activity that may affect their attention to physical activity calorie equivalent labeling. Five hundred mothers will be randomly assigned to enter the study and each 100 one of them will go to one of the five groups. No relevant information regarding use of food labels will be given to mothers, except for two groups. The study groups will be as follows: (1) without nutrition label group, (2) current traffic light label group, (3) physical activity calorie equivalent label group, (4) current traffic light label group with a brochure for more information, and (5) physical activity calorie equivalent label group with a brochure for more information. A “food choice” brochure will be handed to mothers describing the labeling information in detail and the participants will be asked to read it after filling their questionnaires.

We will present products of each groups in one classroom and so, we will have 3 classrooms for participants. The first classroom will include food items “without nutrition label”, the second classroom will be for “current traffic light label” and “current traffic light label group with a brochure for more information” and finally the last classroom will be presented by foods with “physical activity calorie equivalent label” and “physical activity calorie equivalent label group with a brochure”. Milk, yogurt and cheese will be in the dairy group. Due to different brands designs, there will be at least 30 dairy products. Twenty beverages and twenty cakes and biscuits will be shown in other rows. All the foods in five food groups will be similar in brand and type.

Products included in the “without nutrition label” group will provide no nutrition information. There will be no change in the traffic light label group and the labels will appear exactly as produced by factories. Calories and serving sizes of products on labels will be based on factories definition and we do not change them. Each particular food with either no label, or old traffic light label, or our newly designed label will be presented into 3 classrooms similarly. Groups in traffic light label and physical activity calorie equivalent label will only be different in the form of figures and presentation of some information such as physical activity. Finally, the products with physical activity calorie equivalent labels will be covered with the new designed label. Each mother will be asked to imagine she is in a supermarket, choose one product that she wants from each category to buy for her family; place them in a bag inside the room, and then leave there. One of the researchers will record food items. For example, one package of creamy cake has about 320 cal, while there is another cake with only 130 cal; so we expect mothers to choose better option based on the information provided by the labels. Thus, at the end of the study, the total calories from each category as well as the total calories of all selected foods will be compared among different 5 groups. For each of the five groups, the “time” spent by each participant while selecting food items will be recorded by the researcher. After the food choice stage, a series of short questions will be asked in order to assess the mothers’ attention to the mentioned labels. All the collected data will be entered into a database.

Accordingly, the major consequence obtained in this step will show the effect of the new designed label that focuses on the differences in calories for each food group. Accordingly, the major consequence obtains from this step would be the effect of the new label on choosing lower calories goods by consumers and the second outcome would be the time spent while food selection according to different labels.

#### Randomization method in phase 2

Stratified balanced blocked randomization will be applied. Strata are schools, and each of the five blocks consists of ten participants in every school. The blocks and sequence within block will be generated using the Stata Statistical Software and will be given to the person who will manage random allocation of individuals in the school. This method will balance the number of participants in all groups and ensure allocation concealment. The assessor and the analyzer will be blind to groups’ randomization and outcome evaluation.

Mothers will be selected by a person other than the investigator. On the other hand, mothers will select food products while they are alone in the room. The diagram of the intervention phase and the time schedule are shown in Figs. 1 and 2, respectively.

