#### Method of calculating sample size and number

We calculated the number of participants by using G*Power software 3.1 [28]. In this regard power analysis was applied based on a linear multiple regressions with an assumed small to medium effect size (f = 0.18). The total sample size in this case will be 481 with power of 0.9. The sample size is 96 in each arm after attrition, and we scaled that up to *n* = 100 therefore, 500 subjects will be studied in total. Due to the multiple comparisons, alpha level will be adjusted and interpretation of statistically significant results will be done by taking conservative cautions.

#### Qualitative analysis of data in phase 1

The MAXQDA 10 software will be used to analyze the interviews. This software is used to analyze social-oriented texts [29]. Qualitative analysis with thematic approach will be used. It will be done as follow. First, data will be analyzed after each group discussion or interview; for this purpose, all the data will be entered into the software in a textual format. The strengths, weaknesses, description, and information for the new physical activity calorie equivalent label will be defined as categories, and each category will be stored in a special part of the software. Thereafter, decision will be made on coding units after reading the text for several times and the codes will be added to each relevant category at the same page of the software. At this point, classification will be done using the data of the study, and the stability of the coding will be tested. The coding stability will be re-checked after encoding the full text in the software. Finally, the structures of meanings will be provided based on the data inference.

#### Statistical analysis of data in phase 2

Analysis of Variance (ANOVA) will be used to examine the relationship between the label type and the main consequence showing calorie of the selected products and the second outcome which is spent time during food selection. The purpose of this analysis is to see whether the difference between different groups has a significant effect on the main outcome. In order to adjust the effect of confounders (education level, body mass index, age, and socioeconomic status) multiple linear regressions will be used and the energy of the selected food products in each group will be analyzed. In all tests, type I error will be considered 5% and the data will be analyzed using the Stata 12 and SPSS version 16.

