### Limitations

The final stage of the study will be simulating the environment since the mothers are actually in the sample food selection room, which is one of the study limitations. However, for the purpose of examining the effect of labels, there will be a comparison group and since the conditions are the same for all groups, it will largely moderate the conditions. Furthermore, the mothers will be blinded to the main goal of intervention.

Another limitation is assigning the selection process only to mothers and not involving fathers in the study, so that gender differences will not be clear. The reason for targeting the mothers is that they are more involved in purchasing and preparing food and in different studies [32, 33] it has been founded that women use food labels more than men. Due to Iranian previous studies [34, 35] the use of nutrition labels among people was rare. Thus, we decided to consider women who might be more responsible for preparing foods in households.

In the present study health literacy or nutrition knowledge will not be measured whilst nutritionist or food technologist mothers will not enter in our study. Previous studies in Iran did not report any significant variances of knowledge or usage of nutrition labels [34–36].

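### Each label type has its own classroom and no rotation is stated, so every between-label comparison is also a comparison of rooms

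*Protocol article*

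**What the plan says.** Under Phase 2: intervention, the protocol has five groups, and "each 100 one of them will go to one of the five groups". On the display it states: "We will present products of each groups in one classroom and so, we will have 3 classrooms for participants". The first room holds unlabelled products, the second serves both traffic-light arms and the last serves both activity-label arms. The foods are to match in brand and type and to be shown in a similar way in the three rooms. The time "spent by each participant while selecting food items will be recorded by the researcher". The section does not say that labels move between rooms or are assigned to them at random.

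Under Randomization method in phase 2, mothers are individually allocated in blocks within school, and each chooses alone. Under Statistical analysis of data in phase 2, the tests are an ANOVA by label type and a regression adjusting for education, body mass index, age and socioeconomic status. Neither names a room or school term, and "In all tests, type I error will be considered 5"%.

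Under Limitations, the protocol answers the artificial setting by pointing to the comparison group: "since the conditions are the same for all groups, it will largely moderate the conditions".

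**The concern.** Randomising mothers within school balances the mothers over the arms. It does not balance the rooms. Light, space, access and the way the shelves are laid out belong to the classroom, and each classroom carries one label type. Whatever a room adds to the calories chosen or to the time taken is read as an effect of the label.

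Two things can follow. If the room difference repeats from school to school (for example, the same position or set-up always goes with the same label), the label effect is biased and more mothers do not help. If rooms differ haphazardly between schools, there is no fixed bias. But mothers in the same room share an error component that the individual-level ANOVA treats as independent, so the error rate can exceed the stated 5%. The comparison at stake is the trial's central one, activity label against traffic light, together with the time outcome. Equal conditions, on which the limitations section relies, are asserted rather than secured by the layout.

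**Working it through.** **The plan's own figure.** The sample size section works "with an assumed small to medium effect size (f = 0.18") and states: "The total sample size in this case will be 481 with power of 0.9". With five groups, df1 = 4, noncentrality = f² × N and f² = 0.18² = 0.0324, N = 481 gives noncentrality 15.58 and power 0.9005; N = 480 gives 0.8998. So 481 reproduces, and N = 500 gives 0.913. The section then says: "The sample size is 96 in each arm after attrition", raised to 100. This calculation treats all mothers as independent, with no allowance for rooms.

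**Layout.** 500 mothers over 10 schools is 50 per school, hence 10 per arm per school. I take it that each school has its own three rooms. The protocol does not say so; I infer it from allocation being stratified by school.

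**Assumption.** Let r be the share of outcome variance due to classroom within school and s the share due to school, with total variance 1. The protocol gives neither. I take r = 0, 0.01, 0.02 and 0.05.

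**Case A: rooms vary independently between schools.** Compare two arms in different rooms, 100 mothers each.

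- True variance of the difference: 2 × [r/10 + (1 − r − s)/100] = (2/100) × (1 + 9r − s). School cancels because each school contributes equally to both arms.
- Expected ANOVA residual: 1 − (r + s)/11. Each arm has 99 residual df, and the between-school part contributes 10 × 9 = 90 of them, so the factor on r + s is 90/99 = 10/11.
- Ratio of true to reported standard error: k = √[(1 + 9r − s) / (1 − (r + s)/11)].
- Error at nominal 5%: 2 × [1 − Φ(1.96/k)].

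With s = 0:

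| r | variance ratio | k | pairwise error |
|---|---|---|---|
| 0 | 1.000 | 1.00 | 5.0% |
| 0.01 | 1.09/0.9991 = 1.091 | 1.04 | 6.1% |
| 0.02 | 1.18/0.9982 = 1.182 | 1.09 | 7.1% |
| 0.05 | 1.45/0.9955 = 1.457 | 1.21 | 10.4% |

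Simulation of the overall five-arm F test under the null, for the same r, gives roughly 5%, 6 to 7%, 8% and 14%.

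**Effect of school variance.** At r = 0.01 and s = 0.05 the ratio is 1.04/0.9945 = 1.046, k = 1.02 and the error is about 5.5%. At r = 0.01 and s = 0.10 it is 0.99/0.99 = 1, and the error is 5.0%. Setting the ratio to 1 gives s = 10r: the two cancel when the school share is ten times the room share.

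**Case B: the room effect is the same at every school, or one set of rooms serves everyone.** The variance of the difference becomes (2/100) × (1 + 99r) and the residual 1 − r. At r = 0.01, 0.02 and 0.05, k = 1.42, 1.74 and 2.50, with pairwise error of about 17%, 26% and 43%. In simulation, a paired analysis of school means does not repair this (error 15% to 39%), because the repeated difference is part of the estimate itself.

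**Brochure contrasts.** Both arms of a label share a room, so the room effect cancels. Simulated error stays at or below about 5%.

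**The case against.** The protocol does try to make the rooms alike. The foods match, they are to be shown in a similar way, and the traffic-light and activity-label displays are meant to differ only in the label. Mothers choose alone, so nothing passes between them, and room variance may be close to zero. Calling the rooms first, second and last may be no more than a list, and a condensed article may leave the room plan to a fuller document. This stands as a reason to expect a small effect. It does not break the link between label and room: matching products is not matching rooms, and the limitations section leans on equality that nothing in the stated design guarantees.

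A reader might infer more than the text supports, in four ways.

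- That recorder differences are mixed with label effects. No recorder is tied to a room; one researcher may serve all three.
- That the fixed link is stated for every school. The text says only that there are three classrooms.
- That the ANOVA intervals are certainly too narrow. This needs room variance above zero and not offset by school variance left in the residual; at r = 0 there is no error.
- That the error is larger still when both arms of a label are pooled, 200 against 200. The protocol compares five groups and plans no such contrast.

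**Conclusion.** The aliasing is real and follows from the stated layout: no label, traffic light and activity label cannot be told apart from their rooms by any analysis the protocol names. Brochure contrasts within a label are not affected.

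The size is conditional. With separate rooms at each school, no repeating pattern and no school variance, a room share of up to 5% means a true standard error up to about 21% above the reported one, and pairwise error between 5% and 10.4%. School variance lowers these figures and can remove the excess when the room share is small. A room difference that repeats across schools is the more serious case, since it biases the calorie and time results and no model term can take it out afterwards. The documents do not show that such a pattern will occur; they only leave it open. This should be settled before phase 2 starts.

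**What to change.** At each school, draw by lot or rotate which physical classroom carries which label, and record the assignment. Keep one product layout in all three rooms, and do not let any recorder stay with one label. If a single set of rooms serves several schools, move the labels between those rooms from school to school.

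In the phase 2 regression, include school, which is the randomisation stratum, and a classroom-within-school term for between-label contrasts. The model terms address random room variation; only the rotation protects against a repeating room difference. Reword the limitations sentence to say how conditions are kept equal.

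The cost is a simple room rota and possibly somewhat wider between-label intervals. It needs no extra mothers or staff.

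### The plan compares calories per category and in total without saying which is primary, and the category list is not fixed, although the sample size allows for only one outcome at 5%

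*Protocol article*

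**What the plan says.** **Comparisons.** In the section on the phase 2 intervention, each mother takes one product from each category, and "the total calories from each category as well as the total calories of all selected foods will be compared among different 5 groups". Neither comparison is ranked above the other.

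**Main outcome.** The next paragraph describes the major consequence twice. The first sentence speaks of "the effect of the new designed label that focuses on the differences in calories for each food group". The second speaks of "the effect of the new label on choosing lower calories goods by consumers" and names selection time as the second outcome. The abstract's Discussion bases the evaluation on "differences between the calories of selected food groups". The abstract's Methods, by contrast, names a single main outcome, the energy of the selected products, with time as secondary. The section on statistical analysis in phase 2 does the same. Neither says whether that energy is summed over the bag or taken category by category.

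**Categories.** The abstract's Background and Methods name four product types: dairy, beverages, cakes and biscuits. The display described for phase 2 has a dairy group of milk, yogurt and cheese, and then "Twenty beverages and twenty cakes and biscuits will be shown in other rows", which reads as three. The same paragraph also refers to five food groups.

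**Alpha and sample size.** The sample-size section assumes f = 0.18 and power 0.9, reaches 481, and rounds up to 100 per arm (500). It says that alpha will be adjusted because of multiple comparisons. The statistical section then sets the type I error at 5% for every test. No family of tests and no adjustment method is given.

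**The concern.** Calories per category and calories in total are different outcomes and can disagree. A label could lower cake calories and raise dairy calories, leaving the total unchanged. On the per-food-group wording that is an effect on the main outcome; on the total reading it is not. With no ranking, a significant result in any one category, or in the total alone, could be reported as the main finding.

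Two things follow. If each result is tested at 5%, the overall false-positive rate rises above 5%. If alpha is divided over all of them, the planned 500 mothers no longer give the stated power. The article does not say which of these applies. The total is also not fully defined until the list of categories it sums over is fixed.

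**Working it through.** **1. Reproduce the sample size.** Inputs from the sample-size section: f = 0.18, power 0.90, five arms. Alpha is taken as 0.05. For a five-group overall F test, df1 = 4, df2 = N − 5, and the noncentrality is λ = N × f² = N × 0.0324.

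- N = 481: λ = 481 × 0.0324 = 15.58, power 0.9005.
- N = 500: λ = 500 × 0.0324 = 16.20, power 0.913.

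A multiple regression with f² = 0.0324 and four tested predictors also gives 481, with or without four further covariates. Reading 0.18 as f² would give 91, so it was used as f. The figure of 481 is therefore correct for one outcome at unadjusted 5%.

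**2. Count the calorie results that could be called main.** Three categories plus the total make 4. Four categories plus the total make 5. If five food groups is meant literally, there are 6.

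**3. False positives if each is tested at 5%.** If the tests were independent, the chance of at least one is 1 − 0.95^m:

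- m = 4: 18.5%
- m = 5: 22.6%
- m = 6: 26.5%

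The total is the sum of the categories, so the tests are not independent. Null trials were therefore simulated with 5 arms of 100 mothers, normal data and equal variances. Each category and the sum was tested by one-way ANOVA at 5%. The documents give no between-category correlation, so 0 to 0.6 is an assumed range. Each cell shows a run of 20,000 trials and, after the slash, a separate run of 4,000.

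| Assumed correlation | 3 categories + total | 4 categories + total |
|---|---|---|
| 0 | 16.5% / 16.8% | 21.1% / 20.1% |
| 0.3 | 14.9% / 14.1% | 18.6% / 17.9% |
| 0.6 | 12.4% / 13.2% | 15.6% / 14.4% |

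Rounded, this is about 12-17% with three categories and 14-21% with four. Pairwise comparisons between arms and the covariate-adjusted regressions are not counted and would add to it.

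**4. Power if alpha is adjusted.** Bonferroni is used as an example, because the article names no method. Power is for any one given outcome with f = 0.18 at N = 500 (λ = 16.20).

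| Calorie outcomes | Alpha for each | Power at 500 | N for 90% |
|---|---|---|---|
| 1 | 0.05 | 91.3% | 481 |
| 4 | 0.05/4 = 0.0125 | 79.6% | 625 |
| 5 | 0.05/5 = 0.01 | 77.4% | 647 |
| 6 | 0.05/6 = 0.0083 | 75.5% | 665 |

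**The case against.** The best defence is that there is only one main outcome. The abstract's Methods and the statistical section agree on the energy of the selected products, with time second. The category comparisons would then be supporting detail, and a full protocol or analysis plan may say so. The article also promises to adjust alpha. On this view one clarifying sentence is enough, and the sample size stands.

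Much of this is fair. The design is not damaged and 481 is correct. But the conflict lies in what the article states, not in what it leaves out: it compares both sets of calories unranked and ties the major consequence to each food group. The alpha promise does not resolve this, because it names no family, sits beside 5% for all tests, and does not say which result is primary.

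A reader might also infer four stronger things that the documents do not support:

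- **That choosing lower-calorie goods is a third, rival endpoint.** It has no metric of its own, and gives only the expected direction of the same calorie variable.
- **That an uncertain number of items biases the comparison.** The example cakes have about 130 and 320 cal, so one more such item would raise a mother's total noticeably. But every arm chooses from the same categories, so the totals rise in all five arms alike. This alone creates no difference between arms.
- **That there are six competing results.** The mention of five food groups may be a slip for the five study groups. Three versus four categories stays open either way.
- **That the plan as written has a 12-21% error rate.** That follows only if all the calorie tests are run at 5%, and the article also says alpha will be adjusted.

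**Conclusion.** The point holds in limited form. The article does not settle whether the primary outcome is total calories or calories per category, and it describes the category list in ways that do not match. The cost falls on the error rate or on power, depending on which alpha statement is followed: about 12-17% or 14-21% false positives at 5% per test, or about 80% or 77% power at 500 under Bonferroni over four or five outcomes. The first pair rests on assumed correlations of 0 to 0.6, normal data and equal variances. The second rests on f = 0.18 for the outcome in question and on Bonferroni as the example method. The sample size itself is right for a single outcome at 5%. This should be corrected before data collection, but it does not undermine the design.

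**What to change.** - Name one primary outcome. A suitable choice is the total calories of the products each mother places in the bag, one from each category of a single stated list, tested at 5%. This keeps the stated power (about 91% at 500). Per-category calories could be primary instead, but then a multiplicity procedure must be stated and the sample size recalculated.
- Make per-category calories secondary, to show where a change in the total comes from.
- State the category list once and use it throughout: in the abstract's Background and Methods and in the phase 2 display and selection text. Correct or explain the mention of five food groups.
- Reword the two sentences on the major consequence rather than deleting them, because the second also names time as the second outcome. Align the abstract's Discussion and the statistical section with them.
- Reconcile the two alpha statements by saying which tests form the family to be adjusted, by what method, and which single test is made at 5%.

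The cost is wording only. The downside is that an isolated result in one category can no longer be claimed as the main finding.
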